## Methods/design

### Overall Study Design

In this prospective cohort study, consecutive and consenting patients enrolled in the Weight Wise Regional Obesity Program and without a contraindication to surgery will be enrolled. The minimum enrolment sample size will include 150 surgical patients, 200 patients receiving intensive medical therapy and 150 patients wait-listed to enter the clinic (Figure 1). The number of patients enrolled in the medical arm is larger because we anticipate an increased rate of censoring in this study arm, as some of these patients will ultimately undergo bariatric surgery within the two-year follow-up period.

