^1^Health Care Payor perspective includes cost categories 1-6; Public Payor perspective includes cost categories 1-7 and Societal Payor perspective includes all costs.

After informed consent is obtained, baseline data collection for consenting patients will include the following: age, sex, race, marital status, employment status, household income quintile (≤ 20 K, 20-40 K, 40-60 K, 60-80 K, ≥80 K), general medical history and obesity-related comorbidities, smoking status (current, past, never), detailed current and past medications, weight, BMI, waist circumference, blood pressure, fasting lipids, fasting glucose, HbA1c, and liver enzymes.

Body weight will be measured using a validated, calibrated scale to the nearest 0.1 kilogram after the patient has emptied his/her bladder. Subjects will wear light indoor clothing with empty pockets and no shoes. Height will be measured using a wall-mounted stadiometre. A single reading taken using an automated blood pressure monitor and using an appropriately sized blood pressure cuff will be recorded with the subject seated in a chair and after five minutes of rest.

Repeat assessment of blood pressure, body weight, and cardiovascular risk factors (cholesterol profile, glycemic parameters) will be performed at 2 years.

Additional outcomes to be collected every 6 months will include:

1. **Household income and employment status**

2. **Quality of life and utility measurement**: Health related quality of life will be measured using validated, widely-used instruments. Generic and preference-based quality of life will be assessed using the Short Form-12 (SF-12[50]) and the EuroQol-5D (EQ-5D[51]) respectively. Obesity-specific quality of life will be assessed using the Impact of Weight on Quality of Life-Lite (IWQOL-Lite) [52].

3. **Patient satisfaction: **Satisfaction with medical care will be assessed using two questions, which will be rated on a 5-point Likert Scale:

a. The medical care I have been receiving is just about perfect

b. I am dissatisfied with some things about the medical care I received.

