#### Comparisons of Costs Over Three Years Between the Surgical Arm, Medically Treated Controls and Wait-listed Controls

First, descriptive statistics will be used to assess cumulative and incremental costs (by perspective and cost category) in each year using the arithmetic mean and 95% confidence interval for normally distributed variables and median with interquartile ranges for skewed variables. Within and between-group comparisons will be performed. Distributions of cost are often skewed and will be normalized, if necessary, by using log-transformations. Unadjusted analyses of costs will be performed using ANOVA; if cost cannot be normalized then nonparametric (e.g., Kruskal-Wallis) tests will be used. If log-transformation of costs is necessary, Duan's smearing estimator will be used to calculate appropriate error estimates after the data are re-transformed from the logarithmic scale [63].

Second, covariate controlled sequential multiple linear regression models will be constructed to determine the independent association of surgery (versus medical or wait-list controls) on each incremental cost outcome. Cumulative costs over time will be calculated using standardized methods,[64,65]and costs for average hypothetical patients will be calculated using the least squares means method, and adjusted for significant predictor variables for costs for medical and wait-listed controls.

Third, the net economic impact of increasing bariatric surgery rates from a societal, public payor, and health care payor perspective will be assessed using a mathematical model developed by our team. The costs determined above will be input, and the net economic impact of increasing rates of bariatric surgery from current rates (0.1% of eligible patients) to 0.5% (estimated current rates in US), 5% and 10% of all eligible patients will be calculated.

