##### Sample Size Considerations

Using previous estimates,[66] we have adequate power to detect a difference of 20% or greater in costs between the surgical groups and the medical controls or the wait list controls, assuming an average 2-year total incremental cost of $12 183 in surgical patients, a standard deviation of $6000, two sided alpha = 0.05, and beta = 0.90.

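### If costs are log-transformed, least squares means for an average patient fall below the mean cost that the net-impact model needs, by about 2–4% at the protocol's own CV

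*Protocol article*

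**What the plan says.** All of this is in the protocol article, in the section on cost comparisons over three years.

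- **Transformation.** "Distributions of cost are often skewed and will be normalized, if necessary, by using log-transformations". Duan's smearing estimator is to be used on retransformation.
- **Adjusted costs.** Multiple linear regression with covariates estimates the association of surgery with each incremental cost outcome. Then "costs for average hypothetical patients will be calculated using the least squares means method", with adjustment for significant predictors.
- **Use.** "The costs determined above will be input, and the net economic impact of increasing rates of bariatric surgery" from 0.1% of eligible patients to 0.5%, 5% and 10% is to be calculated.

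The section does not name the covariates, say how categorical covariates are weighted, or say which of the cost summaries listed above that sentence is the input.

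**The concern.** A model that multiplies a cost per patient by a number of patients needs the mean cost over those patients. The cost of one hypothetical patient with average characteristics is a different quantity whenever cost is not linear in the covariates. On the log scale it is always the smaller of the two.

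The plan's safeguard, smearing, does not close this gap. Dollar differences between arms would then be too small by the same proportion, and the error would be multiplied up in the extrapolation.

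A second question arises if least squares means give each level of a categorical covariate equal weight. The average patient then has a case mix that the cohort may not have.

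**Working it through.** **Inputs from the protocol.** The cost section's Sample Size Considerations has "assuming an average 2-year total incremental cost of $12 183 in surgical patients, a standard deviation of $6000". The CV is 6,000/12,183 = 0.4925, and the implied lognormal log variance is s² = ln(1 + 0.4925²) = 0.217. Planned enrolment is "150 surgical patients, 200 patients receiving intensive medical therapy and 150 patients wait-listed to enter the clinic".

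**Inputs assumed, because the protocol gives none.** The share of log variance explained by covariates (R²) is 0.2–0.4, with wider values as a check. A CV of 1.0 is tried as an alternative. Costs are lognormal, and there is no arm-by-covariate interaction.

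**1. The plan's own figure.** It claims "adequate power to detect a difference of 20% or greater in costs between the surgical groups and the medical controls", with "two sided alpha = 0.05, and beta = 0.90"; I read the last value as power. The difference is 0.20 × 12,183 = $2,436.60. Then n per arm = 2 × (1.960 + 1.282)² × (6,000/2,436.6)² ≈ 127.4, so 128. Power is 0.940 for 150 v 150 and 0.964 for 150 v 200. The claim reproduces on the enrolled numbers. It says nothing about the least squares means and serves here only to fix the mean and SD.

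**2. Linear model in dollars.** For arm k, the mean over patients of (a_k + b′x_i) equals a_k + b′x̄. At the observed covariate means, the least squares mean is the average predicted cost. The error is exactly 0%.

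**3. Log model with smearing factor S.**

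- Least squares mean: S · exp(a_k) · exp(b′x̄).
- Mean predicted cost: S · exp(a_k) · mean of exp(b′x_i).

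S cancels from the ratio of the two. If b′x is roughly normal with variance R²s², the ratio is exp(−R²s²/2).

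| CV | s² | R² = 0.2 | R² = 0.3 | R² = 0.4 |
|---|---|---|---|---|
| 0.49 (protocol) | 0.217 | −2.1% | −3.2% | −4.3% |
| 1.0 (assumed) | 0.693 | −6.7% | −9.9% | −12.9% |

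At CV 0.49 the wider range R² = 0.05–0.5 gives −0.5% to −5.3%, and a 10% error would need R² = 0.97. A simulation of 150/200/150 patients (400 runs, correct smearing) agrees: −2.13% and −3.11% at R² 0.2 and 0.3 for CV 0.49; −6.39% and −9.15% for CV 1.0.

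**4. Effect on arm comparisons.** Every arm is multiplied by the same factor. The between-arm ratio is unchanged (0.00% in the simulation), and the dollar difference shrinks by that factor. On a difference of $2,436.60, a loss of 2.1–4.3% is about $52–$104 per patient. The Background gives 1.5 million potentially eligible Canadians. Moving from 0.1% to 10% is 9.9% × 1.5 million = 148,500 patients, so the error is about $8–15 million on 148,500 × $2,436.60 ≈ $362 million.

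**5. Equal weighting of categories, if used.** With one assumed 80/20 covariate, CV 0.49 and R² 0.1–0.5, arm costs came out 6.3–12.5% too low in the dollar model and 8.6–20.3% too low in the log model. A different assumed case mix (80% women, 35% diabetic, 65% employed, 12% smokers) gave arm costs 9–14% too high in a log model. The direction therefore depends on the mix. In the additive dollar model the arm difference was unchanged (0.00%).

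**The case against.** The case against giving this much weight is strong, and most of it stands.

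- **The base model is linear, and logging is conditional.** With observed margins the error is then zero. If incremental cost means change from the prior year, which the wording leaves unclear, values can be zero or negative and could not simply be logged. The point therefore applies only on the log branch. The plan does anticipate that branch, and specifies smearing for it.
- **Equal weighting is not stated.** An average patient can as naturally mean one at the observed averages. Sex, race, smoking and income are listed as baseline data, not as cost-model covariates. How margins are weighted is something an article may leave to a fuller plan, so its absence is no criticism.
- **The link to the net-impact model is inferred.** The costs referred to could be arithmetic means, medians, regression increments, cumulative costs or least squares means. The least squares means are, however, the adjusted per-patient costs described immediately before that step, and a median would not scale to a total either.
- **The error is small against sampling error.** The standard error of an arm mean is 6,000/√150 = $490, or 4.0% of $12,183. A 2–4% shortfall is about one standard error or less. It is nevertheless systematic and avoidable.

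A reader might infer that the arm costs are wrong by more than ten percent. The documents do not support that: it needs a CV well above the stated 0.49, or equal weighting of unbalanced categories, and both are assumptions.

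**Conclusion.** The point holds conditionally and is minor. The plan states a method that returns the cost of an average patient, and follows it with a use that needs the average cost of patients. The two agree in a linear dollar-scale model at observed margins. They differ on the log scale, where smearing does not remove the gap.

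The size is about 2–4% at the protocol's own mean and SD with an assumed R² of 0.2–0.4, and 7–13% if the CV is nearer an assumed 1.0. On that branch the dollar difference between arms is understated by the same proportion and the cost ratio is not affected. If categories were weighted equally, arm cost levels could be off in either direction, but the arm difference in an additive dollar model would still be right.

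These sizes rest on lognormal costs, no arm-by-covariate interaction, and the least squares means being what enters the net-impact model. The documents do not show that the economic results will be biased, only that the stated method allows it.

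**What to change.** Replace the least squares means step with standardisation. From the adjusted model, predict each enrolled patient's cost under surgery, under medical care and under waiting. Retransform with smearing if costs were logged, average on the dollar scale, and bootstrap the confidence intervals. State that these averages and their differences are the inputs to the net-impact model. This works for linear and log models alike, and it removes any question about category weights.

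The cost is a few lines of code and a sentence or two in the analysis plan, with no new data. One limit remains: the averages describe the enrolled case mix, which reflects the planned arm sizes, and not all eligible patients. The report should say so when it extrapolates.

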### Outcomes Associated with Bariatric Surgery

Although no large scale, contemporary randomized controlled trials (RCTs) have examined the impact of surgery on cardiovascular morbidity or overall mortality, compelling data are available from high quality observational studies such as the Swedish Obesity Study (SOS), a matched cohort study of 2010 surgical and 2037 controls [16,17]. Compared to the poor long-term results of non-surgical therapy, surgery is the only therapy associated with substantial improvements in weight (averaging 33% after 2-3 years[18] and 16% after 10 years[16]); 15-year mortality rates (5.0% versus 6.3% in well-matched controls; HR 0.71; 95% CI 0.54 to 0.92);[19] 11-year incidence rates of first time cancers (HR 0.67; 95% CI 0.53-0.85);[17] and 7-year mortality rates from coronary artery disease (HR 0.41; 95% CI 0.21-0.78) and cancer (HR 0.40; 95% CI 25-0.65) [20]. In terms of other medical comorbidity, surgery increased remission rates for type 2 diabetes (73% versus 13%; p < 0.001; OR 5.5; 95% CI 2.2-14) in a 60-patient RCT;[21] and meta-analyses of primarily observational data has demonstrated that surgery is associated with resolution or improvement of type 2 diabetes, hypertension, dyslipidemia and sleep apnea in 70-86% of cases [18]. Additional studies demonstrate that surgery significantly (p < 0.05) improves psychosocial functioning,[22] quality of life,[23] and physical function [24].

In terms of Canadian data, a retrospective analysis of 1035 bariatric surgery patients from a single practice in Quebec reported 5-year excess weight losses of 61-75% following gastric bypass and banding [25]. In an earlier study, patients from this bariatric program (n = 1035) were also retrospectively compared with 5746 age and sex-matched controls identified using administrative data claims in Quebec (clinical variables such as height and weight were not available for controls) [26]. Mortality rates over 5 years were markedly lower in the bariatric surgery cohort compared to controls (0.68% versus 6.17%; RR 0.11, 95% CI 0.04-0.27) although the design of this study cannot rule out the very real likelihood that surgical selection bias (i.e., healthier and higher socioeconomic status patients with lower likelihood of surgical complications more likely to receive surgery) explains some if not most of these findings.

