### Eligibility For Surgery

Within the adult specialty clinic, patients receive approximately 24-36 weeks of intensive lifestyle counselling (diet, exercise, behavioural modification), delivered by a multidisciplinary staff (internists, dieticians, nurses, physiotherapists, and psychologists) according to current recommendations [14]. Patients are seen approximately every 4-8 weeks. Patients interested in bariatric surgery are also evaluated for this procedure by the same multidisciplinary staff. Patients deemed to be appropriate candidates are subsequently evaluated by a bariatric surgeon. Patients with BMI levels ≥ 35-39.9 kg/m^2 ^and a major medical comorbidity (e.g., hypertension, type 2 diabetes, sleep apnea) or BMI levels ≥ 40 kg/m^2 ^are considered potential candidates for surgery. Absolute contraindications to surgery include pregnancy, uncontrolled psychiatric disease, active substance abuse or smoking (patients are required to quit prior to surgery), an active eating disorder (anorexia or bulimia), and high-risk for surgery medical status (e.g. severe coronary artery disease). Because of limited data documenting the benefits of surgery in patients younger than 18 years of age and evidence for possible harm in patients over 60,[47] procedures are not performed in these age groups. In order to access surgery, patients are also required to demonstrate commitment to attend scheduled appointments and adhere to lifestyle modification and behavioural therapy.

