4. **Impact of Extended Wait Times: **The Waiting List Impact Questionnaire (WLIQ),[53] is a previously validated 47-item list of open-ended patient statements designed to assess the impact of extended wait-times in Canada for coronary bypass surgery and will be administered to wait-listed patients. This instrument has been modified for use in a bariatric population and items deemed not relevant to the bariatric setting were eliminated, resulting in a 40-item questionnaire. The instrument assesses general quality of life on a scale of 0-100 and also examines specific domains (physical stress, social support, frustration, employment status), which are serially evaluated by patients on a 5-point Likert scale. The degree of interest in bariatric surgery is specifically assessed.

5. **Edmonton Obesity Staging Score (EOSS)**:[54] EOSS is a recently proposed, preliminary staging system for obesity which is based upon the presence or absence of obesity-related comorbities. EOSS will be evaluated as a triage and prognostic tool within the APPLES cohort.

6. **Economic Data **(Table 1): Economic data will be collected for the year prior to enrolment and in the two years following enrolment. Two major data sources will be used to collect economic data.

a. **Administrative Data**: Linkage to AHS and Alberta Health and Wellness (AHW) administrative data sources will be performed according to previously described methods [55,56]. Because all permanent residents of Alberta are eligible for insurance by AHW and over 99.9% participate in this coverage, these administrative data will comprehensively capture patient-specific health care resource utilization. Data elements include vital statistics (mortality) and the following health care resources and costs: inpatient and outpatient encounters, physician billings, medical procedures, and emergency room visits (Table 1).

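### The adjusted mean costs are tied to significant predictors, a rule that can drop real confounders in this non-randomised comparison

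*Protocol article*

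**What the plan says.** The section Comparisons of Costs Over Three Years Between the Surgical Arm, Medically Treated Controls and Wait-listed Controls describes two adjusted steps after the descriptive one.

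- For the surgery effect, "covariate controlled sequential multiple linear regression models will be constructed to determine the independent association of surgery". The covariates are not named, and no criterion for choosing them is attached to this step.
- Costs for a typical patient are then obtained as least squares means, "adjusted for significant predictor variables for costs for medical and wait-listed controls". No threshold or selection procedure is given.

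The costs from these steps are then put into a model of the net economic impact of raising surgery rates to 0.5%, 5% and 10% of eligible patients.

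Three other parts of the article bear on the rule.

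- The design is observational: "In this prospective cohort study, consecutive and consenting patients enrolled in the Weight Wise Regional Obesity Program" are enrolled, without randomisation (Overall Study Design).
- Entry to surgery is selective: "patients are also required to demonstrate commitment to attend scheduled appointments and adhere to lifestyle modification and behavioural therapy" (Eligibility For Surgery). Of an earlier Quebec cohort the authors write that "the design of this study cannot rule out the very real likelihood that surgical selection bias" explains part or most of the result (Outcomes Associated with Bariatric Surgery).
- Baseline data include "age, sex, race, marital status, employment status, household income quintile", comorbidity, smoking and BMI, and "Economic data will be collected for the year prior to enrolment and in the two years following enrolment" (Data Collection and Outcome Measures).

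**The concern.** In a randomised trial, choosing covariates by significance mainly affects precision. Here it affects validity. A variable confounds because it differs between arms and also affects cost. Its own p-value in a few hundred patients measures only the second link, and measures it with noise. A moderate predictor of cost that is clearly imbalanced can miss the threshold and be dropped, and its imbalance is then counted as a surgery effect. If the reduced model is treated as though it had been fixed beforehand, its standard error also ignores the selection.

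Objective 3 hypothesises lower total costs for surgery, and the Discussion says that cost savings or neutrality for the public payor would make expansion a priority. Residual selection bias in the adjusted means would carry into the impact model. Its direction is not known. If selection works here as the authors suspect it did in Quebec, with healthier and better-off patients operated on, it would favour surgery.

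**Working it through.** **The plan's own figure.** Inputs from Sample Size Considerations under the cost section: mean $12 183, SD $6000, difference 20%, two-sided alpha 0.05, beta 0.90 (read as 90% power). Group sizes 150 surgical, 200 medical and 150 wait-listed come from Overall Study Design.

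- Target difference: 0.20 × 12 183 = $2436.60.
- n per arm = 2(z₀.₉₇₅ + z₀.₉₀)² × SD² / difference² = 2 × (1.960 + 1.282)² × 6000² / 2436.6² = 2 × 10.507 × 6.064 = 127.4, so 128.
- Power = Φ(difference / [SD × √(1/n₁ + 1/n₀)] − 1.96). For 150 v 150: Φ(2436.6/692.8 − 1.96) = 94.0%. For 150 v 200: Φ(2436.6/648.1 − 1.96) = 96.4%.

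The power statement therefore holds at full enrolment, and this point does not touch it. It supplies the yardstick of $2437.

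**Simulation, surgery v medical.** The following are assumptions, since the article gives no values for them:

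- five independent confounders, each shifted between arms by 0, 0.3 or 0.5 SD;
- each worth 0, 0.10, 0.15 or 0.30 of the $6000 SD in cost;
- residual SD $6000 and no true surgery effect;
- the screen is backward elimination at p<0.05;
- 2000 runs per setting.

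The model is cost = β₀ + τ·surgery + Σγⱼ·Zⱼ + error, with τ = 0. As a check, unadjusted bias should be 5 × imbalance × effect × 6000. For 0.3 and 0.10 that is $900 (simulated $911). For 0.5 and 0.10 it is $1500 (simulated $1506).

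| Patients | Imbalance (SD) | Effect (SD of cost) | Confounders kept | Bias, screened | True SD | Mean reported SE | Coverage, screened | Coverage, all forced in |
|---|---|---|---|---|---|---|---|---|
| 150 v 200 | 0.3 | 0.10 | 45% | $319 | 725 | 668 | 90.1% | 95.1% |
| 150 v 200 | 0.3 | 0.15 | 79% | $115 | 726 | 681 | 92.8% | 95.3% |
| 150 v 200 | 0.5 | 0.10 | 45% | $506 | 828 | 695 | 83.5% | 94.9% |
| 150 v 200 | 0.5 | 0.15 | 79% | $232 | 861 | 727 | 89.1% | 94.6% |
| 105 v 140 | 0.3 | 0.10 | 34% | $363 | 855 | 794 | 90.2% | 95.1% |
| 105 v 140 | 0.3 | 0.15 | 63% | $261 | 854 | 809 | 91.8% | 95.6% |
| 105 v 140 | 0.5 | 0.10 | 34% | $628 | 963 | 819 | 82.9% | 95.5% |
| 105 v 140 | 0.5 | 0.15 | 64% | $426 | 1021 | 854 | 87.2% | 95.0% |

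Simulation error is about √(0.95 × 0.05/2000) = 0.5 points for coverage and at most 1021/√2000 = $23 for bias. With all five confounders forced in, bias stays within $35 and coverage is 94-96% in every setting run. Against the target, the screened bias runs from 115/2437 = 5% to 628/2437 = 26%.

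**Where the rule does no harm.** With confounders worth 0.30 SD of cost each, the screen keeps 99-100% of them, bias is at most $23 and coverage is 94-95%. With no imbalance, bias is at most $29 and coverage 94-96%.

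**Bias or narrow intervals?** Take 150 v 200, imbalance 0.5, effect 0.10. With no bias but the understated SE, the limits are 1.96 × 695/828 = 1.645 true SDs, giving 90.0% coverage. With a correct SE but the bias, 506/828 = 0.611, coverage is Φ(1.349) − Φ(−2.571) = 90.6%. Together they give Φ(1.034) − Φ(−2.256) = 83.7%, matching the simulated 83.5%. The two causes contribute about equally here.

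**The case against.** The strongest objection is scope. The quoted rule sits in the sentence on least squares means. The surgery effect comes from the separate regressions, and nothing says that those are screened. A reader might infer that all the cost models adjust only for significant predictors, so that the estimate deciding Objective 3 is known to be biased. The article does not support that: the regressions may carry covariates whatever their p-values. What remains is that significance is the only criterion the section states, and that the adjusted means are among the costs passed to the impact model.

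A reader might also infer that stated confidence intervals fail to reach 95%. The section's only 95% interval belongs to the descriptive step. None is specified for the adjusted estimates, so the coverage figures describe what would happen if intervals were computed in the usual way. Nor is narrowness the whole mechanism, since much of the coverage loss is bias.

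The wording might be read as selecting predictors in the controls alone. The phrase can equally name the groups whose costs are calculated, so no error is shown there.

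The threshold, the procedure and the confounder strengths are assumptions. The 30% attrition behind 105 v 140 is given for quality of life and weight, not costs. Hospital, outpatient and physician costs come from administrative data with over 99.9% population coverage, so 105 v 140 is pessimistic for them. It is more plausible for the interview-based categories in Table 1. That objection stands, and 150 v 200 is the fairer base case for administrative costs.

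Finally, an article may leave its covariate list to a fuller document, so the missing list is no fault. The stated rule is different: a fuller plan that followed the sentence would inherit it.

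**Conclusion.** The point holds for the adjusted mean costs, as a conditional risk. The article sets a significance criterion where confounding is the main threat, in a setting where it names selection into surgery as a serious problem in comparable work. Under a p<0.05 backward screen with modest, imbalanced confounders, bias is roughly $100-600 (5-26% of the $2437 target difference) and nominal 95% intervals would cover roughly 83-93%. With strong confounders or balanced arms the harm vanishes. The article cannot tell us which case applies. The rule is still worth replacing, because the fixed set kept bias negligible and coverage near 95% in every setting examined.

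**What to change.** In the cost-comparison section, replace the significance rule with wording such as: *All cost regressions and least squares means will include the same baseline covariates, chosen in advance and retained whatever their p-values, for every arm: cost in the year before enrolment, age, sex, BMI, comorbidity (or the baseline EOSS stage), smoking, employment and income band.* EOSS is also listed among the six-monthly outcomes, so only its baseline value should be used. With prior-year cost as a covariate, the outcome is best taken as cost after enrolment, which avoids having the same year on both sides of a log-scale model.

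No new data are needed. Coding the set as single terms except smoking (three categories) and income (five bands) takes 6 + 2 + 4 = 12 parameters, against 350 patients in surgery v medical. The cost is precision if the covariates prove irrelevant. In the simulation at 150 v 200 with confounders that had no effect on cost, the fixed model's SD was 672 v 644 (4% larger) at 0.3 SD imbalance and 750 v 682 (10% larger) at 0.5. With modest real confounders at 0.5 SD imbalance the fixed model was the more precise one: 749-761 v 828-861.
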